Patients with suspected acute stroke will undergo diagnostic procedures and management according to usual clinical care. LF-MRI will be performed on admission, 24 hours, 72 hours, at the hospital discharge and 4 weeks after the event. LF-MRI findings will not be used to make clinical decisions on patients’ management. Every time a stroke dispatch is activated, the dedicated research staff will be alerted by the local neurologist on duty. The research staff will check eligibility criteria, obtain informed consent and perform study procedures independently of the personnel in charge of managing the acute stroke case. All included patients with suspected stroke will be managed and treated per usual care by the hospital staff not involved in study procedures. Conventional stroke imaging will be performed as needed according to current clinical practice (non-contrast CT+CT angiography and/or HF-MRI+MRI angiography in selected cases, with/without CT or HF-MRI perfusion study).

For the aim of the study, all included patients will be investigated with LF-MRI at predefined time points (24 hours, 72 hours, hospital discharge, 4 weeks). The acquisition of LF-MRI will be performed by a dedicated study staff that will be distinct from the clinical staff involved in the care of the acute stroke patient, thus not subtracting time or resources to usual care. Information obtained by LF-MRI will not be used to take clinical decisions regarding further investigations or treatment. Due to feasibility reasons, the study will include only patients presenting to the ED with suspected stroke during weekdays daytime hours. Study procedures are summarised in figure 1.

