### LF-MRI equipment and imaging protocol

Three FDA and EU approved portable LF-MRI commercialised by Hyperfine Research (www.hyperfine.io) will be employed. All patients will be preliminarily tested with a metal detector to ensure the absence of potentially interfering ferromagnetic devices throughout the body. Patients will undergo LF-MRI directly in the CT suite during the downtime of preparation which usually occurs after urgent CT imaging (current mean door-to-imaging time: **~**20–25 min), thus not delaying the conventional diagnostic process and treatment administration. Specifically, LF-MRI acquisition will be performed during the time needed to obtain the neuroradiological report, waiting for results of essential laboratory tests, stroke nurse arrival, IVT initiation and/or preparation of the angiography room. For patients eligible for immediate IVT following brain CT, LF-MRI will be conducted simultaneously during the administration of IVT. In cases where acquisition of images with LF-MRI is supposed to delay initiation of revascularisation procedures, study procedures will be stopped and the patient will be excluded from the study. LF-MRI will also be repeated by the study staff at predefined time points: 24 hours, 72 hours, at the discharge and 4 weeks after the event.

A prespecified acquisition of Fast-Spin Echo essential stroke sequences will be performed, starting with DWI, apparent diffusion coefficient (ADC) mapping and FLAIR. Other sequences will be performed based on DWI (ADC) and FLAIR findings and on clinical information (suspected stroke subtypes, eligibility to reperfusion treatment), to shorten the duration of LF-MRI acquisition and avoid treatment delay. The prespecified LF-MRI minimum acquisition time pulse sequences protocol is displayed in figure 2. Furthermore, an angiographic sequence will be tested to assess the presence of cerebral LVO or stenosis. This sequence will evaluate the loss of signal due to blood flow in the time frame between the excitation pulse and signal refocusing. Overall, LF-MRI acquisition has been set up to require ~20–25 min to complete, as estimated using the Hyperfine model of portable LF-MRI.

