Detection of lesions at LF-MRI versus non-contrast CT: to compare the accuracy of LF-MRI scans with the accuracy of routinely performed head CT scans for infarcts and haemorrhage detection (endpoint: agreement between LF-MRI and head CT scans in detecting infarcts and haemorrhages).Detection of lesions at LF-MRI versus HF-MRI: to compare the accuracy of LF-MRI scans with the accuracy of routinely performed brain HF-MRI scans for infarcts and haemorrhage detection (endpoint: agreement between LF-MRI and HF-MRI scans in detecting infarcts and haemorrhages).Treatment decision-making based on LF-MRI: to evaluate the impact of LF-MRI on the clinical decision-making process related to revascularisation treatments for ischaemic stroke, as compared with the conventional acute stroke diagnostic (endpoint: agreement between the best treatment option based on LF-MRI and the best treatment option based on conventional imaging).Impact of LF-MRI implementation on the door-to-needle time (DTNT) in patients eligible to IVT: to evaluate whether the implementation of LF-MRI may impact on the DTNT in patients treated with IVT at each recruiting site (endpoint: comparison between the mean DTNT recorded during the 2 months before the protocol initiation—and in patients who refuse to undergo LF-MRI during the study period—and the mean DTNT estimated basing on the results of LF-MRI).Early identification of stroke mimics with LF-MRI: to assess whether LF-MRI may improve the detection of patients with stroke mimics in the acute phase and the discrimination with acute ischaemic stroke (endpoint: agreement between LF-MRI and conventional imaging in detecting stroke mimics).Agreement between LF-MRI and conventional brain imaging at different post-stroke time points: to assess the performance of LF-MRI at different phases of the ischaemic stroke process (hyperacute, acute—24 hours, subacute—72 hours and chronic—4 weeks from the event) and to compare with findings from conventional neuroimaging (endpoint: agreement between LF-MRI and conventional neuroimaging at different stroke phases).

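### The door-to-needle comparison is not like for like: a recorded historical mean and refusers are set against an estimated time in a differently selected group

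*Protocol article*

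**What the plan says.** All places are in the protocol article.

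- **Outcomes measurement.** The DTNT outcome asks whether implementing LF-MRI affects DTNT in patients given intravenous thrombolysis (IVT) at each recruiting site. The endpoint is a "comparison between the mean DTNT recorded during the 2 months before the protocol initiation" "and in patients who refuse to undergo LF-MRI during the study period", set against "the mean DTNT estimated basing on the results of LF-MRI".
- **Study design.** For feasibility, "the study will include only patients presenting to the ED with suspected stroke during weekdays daytime hours". The same section says that "LF-MRI findings will not be used to make clinical decisions on patients’ management".
- **LF-MRI equipment and imaging protocol.** The scan follows CT and uses preparation downtime. In patients eligible for immediate IVT, "LF-MRI will be conducted simultaneously during the administration of IVT". Where the scan is expected to hold up revascularisation, "study procedures will be stopped and the patient will be excluded from the study". Acquisition is planned to take about 20–25 min.
- **Time points and collected variables.** The actual door-to-needle time and the LF-MRI scan duration are both recorded in the hyperacute phase.
- **Study period.** The study started on 13 February 2023. Enrolment runs from 1 February 2024 to 31 January 2027.

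**The concern.** The endpoint is meant to show whether bringing LF-MRI into the acute pathway changes the time to thrombolysis. The article's own Box 1 lists that impact as unknown. A before-and-during comparison can address it only if both sides measure the same quantity in similar patients over defined periods. Here the quantity differs (recorded against estimated), the stated selection rules differ (hours of arrival, removal for expected delay, consent or refusal), and the start of the baseline is open to two readings.

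If the plan is followed as written, a finding of no difference in DTNT would not show that LF-MRI leaves treatment times unchanged, and a finding of a difference could not be attributed to LF-MRI.

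**Working it through.** **1. Is there a figure to reproduce?** No. The sample size section gives 273 patients for accuracy and 214 for kappa. Neither concerns DTNT. No SD, margin, expected difference or number of IVT patients is given for this outcome.

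**2. The two sides compared**

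| Feature | Comparator | LF-MRI side |
|---|---|---|
| Value | Recorded DTNT | Estimated DTNT |
| Arrival hours | None stated for the historical part | Weekday daytime |
| Removal for expected delay | None stated | Yes |
| Consent | Historical patients, plus refusers | Consenting patients |
| Calendar period | Two months before an undefined date, plus concurrent refusers | 1 February 2024 to 31 January 2027 |

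**3. Recorded against estimated.** Let B be the comparator mean, M_obs the observed mean in LF-MRI patients and M_est the estimated mean. Then

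M_est − B = (M_est − M_obs) + (M_obs − B).

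The first term is a hypothetical shift produced by the estimation. Only the second can carry an effect of having the scan in the pathway. The endpoint reports the sum. When the scan runs during IVT its result cannot precede the needle, so in those patients M_est is necessarily counterfactual.

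**4. The exclusion for expected delay.** Let e be the share of IVT patients removed, D the scan-related delay in them and R the delay in those kept. The mean delay in all is e·D + (1 − e)·R, but those kept show only R. The unseen part is e·(D − R), which is positive whenever D > R, and the rule selects patients on that expectation. The document gives neither e nor D, so no size follows. Because the scan is stopped, the delay actually incurred may be small.

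**5. Time of day (illustration, all inputs assumed).** Let f be the off-hours share of the baseline and d the off-hours minus daytime mean DTNT. The baseline then exceeds a weekday-daytime baseline by f·d.

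- f = 0.4, d = 5 min: 0.4 × 5 = 2 min.
- f = 0.7, d = 20 min: 0.7 × 20 = 14 min.
- f = 0 or d = 0: 0 min. A negative d reverses the sign.

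If weekday-daytime refusers were pooled into the comparator with share r, this becomes (1 − r)·f·d. With f = 0.6, the unpooled range for d = 5 to 20 min is 3 to 12 min. Pooling gives 0.5 × 0.6 × 5 = 1.5 min at the low end (r = 0.5) and 0.9 × 0.6 × 20 = 10.8 min at the high end (r = 0.1). Pooling would shrink this component.

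**6. Baseline date.** If initiation means 13 February 2023, the baseline ends 353 days before enrolment opens and almost four years before it closes. If it means 1 February 2024, the baseline directly precedes enrolment. The first reading leaves more room for secular change in DTNT.

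**The case against.** The strongest reply is that an estimated DTNT is a coherent endpoint for a different question: how fast treatment could start if LF-MRI were the decision tool. Because LF-MRI does not guide care, the observed DTNT reflects the burden of study procedures, not decisions based on LF-MRI. That is fair, and it is a reason to keep the modelled value. It does not rescue the comparison, which is presented as the impact of implementation and subtracts a recorded mean from a modelled one.

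A reader might also infer stronger claims that the document does not support:

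- *That the baseline covers all hours.* The article states no restriction, but it does not say all hours either. A filter may exist in the full protocol.
- *That refusers are pooled with the historical patients.* The wording also allows a second, separate comparator. Pooled weekday-daytime refusers would dilute a time-of-day bias, although they remain self-selected.
- *That a delay of 20–25 min would be largely masked.* This treats the scan as a serial delay, whereas the article places it in downtime or during IVT and stops it if delay is expected. The off-hours figures are assumed in any case.
- *That means are imposed on a skewed variable.* The statistical plan chooses mean or median by distribution for description, which largely meets this.

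Separate study staff and the stopping of study procedures also address treatment delay directly, so this outcome is not the only protection.

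**Conclusion.** The point holds as a problem of comparability. Four features rest on the article's own text and need no outside figure: recorded against estimated times, an hours restriction stated for one side only, a delay-related exclusion stated for one side only, and an undefined baseline date. Together they mean that the endpoint as defined cannot show whether LF-MRI changes DTNT.

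A bias towards showing no delay is plausible, chiefly because the exclusion partly designs delay out of the study group. It is not established. Its size depends on the number of patients removed and their delay, neither of which is given, and the direction of the estimated DTNT is unknown because the article does not describe its derivation. The 2–14 min time-of-day range is illustrative only and falls to zero if the baseline is already restricted or if hours do not matter.

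This is one of six secondary outcomes. It does not drive the sample size, and the primary sensitivity and specificity endpoint is unaffected. It should be corrected, but it does not threaten the trial's main conclusion.

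**What to change.** 1. Restrict the historical baseline to IVT patients who arrived in the same weekday-daytime hours and met the same eligibility criteria. Name its dates, in a window just before enrolment opened on 1 February 2024.
2. Make the implementation comparison with the observed DTNT already collected, by site, and report the difference with a 95% CI.
3. For this outcome, keep the consented IVT patients whose LF-MRI was stopped because of expected delay. The imaging section excludes them from the study, so the two passages must be reconciled. This concerns the analysis set only and leaves the conduct of care as it is.
4. Show refusers as a separate concurrent group.
5. Report the LF-MRI-based DTNT separately, labelled as modelled and with its derivation described, not as the tested implementation effect.

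The cost is a filter on routine hospital records and a rewording of the endpoint. The downside is fewer baseline cases, which a longer window from the same records would offset.

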Accurate stroke diagnosis involves distinguishing between ischaemic lesions and intracerebral haemorrhage (ICH), a critical step in assessing patients’ eligibility for IVT. Additionally, ischaemic stroke must be differentiated from common mimics (eg, migraine, seizures, metabolic and functional disorders). Neuroimaging of acute stroke usually involves brain CT, which shows excellent accuracy in detecting ICH (~100%).^6^ However, high-field (HF) MRI currently yields the highest sensitivity and specificity in detecting acute ischaemic lesions. Specifically, diffusion-weighted imaging (DWI) becomes abnormal within few minutes of ischaemic stroke and has shown 86%–100% specificity and 73%–92% sensitivity (98% accuracy) in detecting early ischaemic lesions.^7^ Over the next hours, further ischaemic injury leads to vasogenic oedema, which is visible on fluid-attenuated inversion recovery (FLAIR) sequences. FLAIR offers a sensitivity of 90% in the acute phase and 88% in the subacute phase in detecting brain ischaemic changes.^8^

Advanced brain imaging modalities such as perfusion CT and perfusion-diffusion MRI can identify salvageable brain tissue, potentially extending the time window for reperfusion. Indeed, patients with viable brain tissue at CT perfusion or perfusion-diffusion MRI can benefit from IVT administered up to 9 hours of ischaemic stroke onset,^4^ and from EVT performed up to 24 hours (in patients with anterior circulation LVO).^9^ Additionally, MRI-guided IVT has been shown to significantly improve the functional outcome of patients with stroke of unknown onset who have an ischaemic lesion visible on DWI but no parenchymal hyperintensity on FLAIR.^10^

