### Statistical plan

Categorical variables will be presented as frequency and percentage (%). Continuous variables will be presented as mean (±SD) or median (IQR), according to their distribution. The Shapiro-Wilk test will be performed to assess the normality of variables. Comparison between categorical variables will be performed using the Pearson χ^2^ test, while continuous variables will be compared using the Student’s t-test or the analysis of variance test depending on group numerosity. For comparison including more than two groups, a post hoc analysis will be performed. Initially, a comprehensive description of LF-MRI findings will be provided. LF-MRI diagnostic accuracy will be assessed as sensitivity and specificity, which in turn will be calculated based on the proportion of true/false positives and true/false negatives in respect to the gold standard (ie, the final adjudication of the event, based on clinical and radiological examinations). Positive and negative predictive values will also be calculated. Agreement between LF-MRI and conventional neuroimaging will be evaluated using the Cohen kappa coefficient. The statistical significance will be set at p<0.05.

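### The stroke-mimic outcome and the CT outcome for infarcts ask about accuracy but are scored only as agreement (Cohen kappa), which cannot show which modality is right

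*Protocol article*

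**What the plan says.** All references are to the protocol article.

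- **Mimic outcome (Outcomes measurement).** The aim is "to assess whether LF-MRI may improve the detection of patients with stroke mimics in the acute phase". The endpoint is "agreement between LF-MRI and conventional imaging in detecting stroke mimics".
- **CT outcome (Outcomes measurement).** The aim is "to compare the accuracy of LF-MRI scans with the accuracy of routinely performed head CT scans for infarcts and haemorrhage detection". It is scored as "endpoint: agreement between LF-MRI and head CT scans in detecting infarcts and haemorrhages".
- **Statistic (Statistical plan).** "Agreement between LF-MRI and conventional neuroimaging will be evaluated using the Cohen kappa coefficient".
- **Reference standard (Statistical plan).** The gold standard is "the final adjudication of the event, based on clinical and radiological examinations". It is named for the sensitivity and specificity of LF-MRI only. No sensitivity or specificity of CT or of conventional imaging against it is stated, and no paired comparison.
- **Expected difference between modalities (Introduction).** HF-MRI "currently yields the highest sensitivity and specificity in detecting acute ischaemic lesions". CT is credited with about 100% accuracy for intracerebral haemorrhage.

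**The concern.** Each of the two outcomes puts an accuracy question and answers it with a statistic that contains no truth. Whether LF-MRI improves on conventional imaging depends on who is right when the two disagree. Kappa counts the disagreements and does not ask. It reaches 1 only if LF-MRI repeats every conventional call, errors included.

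For infarcts this matters because the Introduction does not treat CT as the best test for early ischaemia, so informative disagreement is to be expected. The risk lies in interpretation: a modest kappa may be reported as weak performance when the disagreements favour LF-MRI, and a high kappa may be reported as success although it says nothing about improvement.

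**Working it through.** **The plan's own figure.** The nearest number is n=214 for agreement (Sample size calculation: expected kappa 0.8, outcome about 20%, power 80%, dropout about 10%). The null kappa is not given; I assume 0.6, two-sided alpha 0.05, and the goodness-of-fit method for a binary kappa.
- Probabilities of both positive, discordant and both negative: 0.136, 0.128, 0.736 at kappa 0.6; 0.168, 0.064, 0.768 at kappa 0.8.
- Sum of squared differences over null values: 0.00753 + 0.03200 + 0.00139 = 0.04092.
- n = (1.960 + 0.842)² / 0.04092 = 191.8, so 192; 192/0.9 = 213.3, so 214.

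The figure reproduces under that assumption. It sizes agreement, not a difference in accuracy.

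**Formula.** kappa = (po − pe)/(1 − pe), where po is observed and pe is chance agreement. Errors are taken as independent given true status.

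**Inputs from the article.** Stroke prevalence 80%, mimics 20%, LF-MRI about 90% sensitive and 80% specific, N=300 (Sample size calculation); ischaemic share of strokes about 71% (Introduction). Comparator accuracies are my assumptions.

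**1. Symmetry.** LF-MRI at 90%/80% against a comparator assumed at 60%/98%, 80% stroke:
- po = 0.8(0.9×0.6 + 0.1×0.4) + 0.2(0.8×0.98 + 0.2×0.02) = 0.6216
- Positive fractions 0.760 and 0.484; pe = 0.760×0.484 + 0.240×0.516 = 0.4917
- kappa = 0.1299/0.5083 = 0.256

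Exchanging the two modalities gives 0.256 again. In 300 patients, LF-MRI is right and the comparator wrong in about 300[0.8×0.9×0.4 + 0.2×0.8×0.02] = 87. The reverse holds in about 300[0.8×0.1×0.6 + 0.2×0.2×0.98] = 26. Kappa treats both groups alike.

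**2. Infarcts versus CT, perfect LF-MRI.** Infarct prevalence 0.8×0.71 = 0.568; CT specificity assumed 95%.
- CT sensitivity 30%: po = 0.1704 + 0.4104 = 0.5808; CT positive 0.1920; pe = 0.568×0.1920 + 0.432×0.8080 = 0.4581; kappa = 0.1227/0.5419 = 0.23.
- CT sensitivity 60%: po = 0.3408 + 0.4104 = 0.7512; CT positive 0.3624; pe = 0.4813; kappa = 0.2699/0.5187 = 0.52.

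**3. Mimics, perfect LF-MRI.** Conventional adjudication assumed 95% specific.
- Sensitivity 90%: po = 0.72 + 0.19 = 0.91; pe = 0.8×0.73 + 0.2×0.27 = 0.638; kappa = 0.272/0.362 = 0.75.
- Sensitivity 95%: po = 0.76 + 0.19 = 0.95; pe = 0.8×0.77 + 0.2×0.23 = 0.662; kappa = 0.288/0.338 = 0.85.

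Every disagreement in steps 2 and 3 is one where LF-MRI is right.

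**4. Direction.** LF-MRI at 90%/80% against the 90%/95% comparator of step 3: po = 0.8×0.82 + 0.2×0.77 = 0.81; pe = 0.76×0.73 + 0.24×0.27 = 0.6196; kappa = 0.1904/0.3804 = 0.50. A perfect LF-MRI scores 0.75. Kappa rises as LF-MRI improves, but it is capped by the comparator's errors.

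**5. Precision of a paired comparison in mimics.** 20% of 300 = 60 mimics, or 54 after 10% dropout. The 95% half-width is about 1.96√(d/n), with d the discordant share and a difference near zero. For d = 0.20, n = 60 it is 0.113; for d = 0.30, n = 54 it is 0.146. That is about 11 to 15 percentage points; d is assumed.

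**The case against.** **Much of the answer is already planned.** The primary outcome scores LF-MRI against the final adjudication, and mimic is one of its categories, so LF-MRI's specificity is already the share of mimics correctly called. The Sample size calculation says that n=273 serves also for comparison with conventional neuroimaging. The matching figure for conventional imaging may be in a SAP that is not shown. This stands in part: half of the comparison exists. But the article itself names the endpoints and the statistic, and a SAP that followed them faithfully would analyse agreement.

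**Four stronger readings are tempting and not supported.**
- *Any improvement in LF-MRI lowers kappa.* Step 4 shows otherwise. Only cases where LF-MRI corrects a conventional error lower it. The endpoint is uninformative about direction, not reversed.
- *Mimic kappa would be very low even for a perfect LF-MRI.* Modelling the comparator as a bare CT read with infarct sensitivity of 30-60% gives 0.26 to 0.47. But Study design and Outcomes measurement describe conventional adjudication as clinical data plus CT with CT angiography and/or HF-MRI with MR angiography. A negative early CT need not lead to a call of mimic.
- *The whole CT outcome fails.* With CT at about 100% accuracy for intracerebral haemorrhage, agreement with CT is close to accuracy there.
- *The HF-MRI outcome is equally affected.* Its wording has the same mismatch. At the HF-MRI accuracies in the Sample size calculation (91-100% and 86-100%), a perfect LF-MRI scores about 0.71 to 1.00 at 80% stroke prevalence, so the effect is smaller.

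**Independence is unrealistic.** Both readings use the same clinical data, so errors are probably correlated and actual kappas may be higher. That changes the size, not the logic.

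**Conclusion.** The concern holds for the mimic outcome and for infarct detection versus CT. In both, aim and endpoint do not match, and the endpoint as written cannot answer the question put. This follows from the symmetry of kappa and needs no numerical assumption.

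The ceilings (about 0.23-0.52 for infarcts, about 0.75-0.85 for mimics) are illustrations. They rest on comparator accuracies that the article does not give and on conditional independence, and should not be read as predictions.

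The outcomes are secondary. The primary endpoint, the sample size and the conduct of the trial are unaffected. A reader might infer a critical defect; the document does not support that. It should be fixed.

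**What to change.** For the mimic outcome and for infarct detection versus CT:
1. Score LF-MRI and the conventional reading each against the final adjudication (ischaemic stroke, ICH, SAH or mimic).
2. Report the within-patient difference in sensitivity and specificity with a paired 95% CI.
3. Report the discordant cells: LF-MRI right with the comparator wrong, and the reverse.
4. Keep kappa as description. Agreement with CT may remain the endpoint for intracerebral haemorrhage.

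**Cost.** Revised endpoint wording and a few lines of analysis. The separate blinded readings and the final adjudication are already planned.

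**Limits to state alongside.**
- The final adjudication draws on radiology and may favour conventional imaging.
- Infarct status from follow-up imaging can serve as the reference only where that imaging was done, since conventional imaging is performed as needed.
- The mimic comparison rests on about 54 to 60 patients, so only a fairly large difference will be distinguishable from none.
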